### Results dissemination

Throughout the project, regular communication with local government and other regional stakeholders will take place to share progress updates. Interim and final trial results will also be communicated to AKHS,P and GB district health leadership. The study team will recommend that GB district health leadership share findings from the study with LHSs, who will relay results to LHWs, who may then communicate findings to households across GB during home visits.

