### Data monitoring & interim analysis

A data and safety monitoring board (DSMB) comprised of professionals with expertise in neonatal and child health will oversee the safety of the trial. Each DSMB member will be independently responsible for making recommendations for stopping the study based on specific safety endpoints.

Biannual interim analyses will examine the primary and secondary outcomes as well as iNCK compliance measures. The DSMB will convene annually, and at least two weeks prior to each meeting, the panel members will be given a written report outlining the current status of the study, masked outcome data, and information pertaining to any adverse events that may have occurred. If the mortality difference becomes higher than 40% in either direction (i.e., 40% greater mortality in the intervention or control clusters), the DSMB will be unmasked, and a decision will be made on whether the trial should continue.

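### The dissemination plan commits to giving interim trial results to AKHS,P and district health leadership without limiting them to pooled or masked data

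*Protocol article*

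**What the plan says.** Three sentences in Results dissemination matter. The first covers routine contact: "Throughout the project, regular communication with local government and other regional stakeholders will take place to share progress updates". The second adds results: "Interim and final trial results will also be communicated to AKHS,P and GB district health leadership". The third sets out an onward chain, which the team intends to suggest to the district leaders: "share findings from the study with LHSs, who will relay results to LHWs, who may then communicate findings to households across GB during home visits".

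Data monitoring & interim analysis describes what the interim analyses contain: "Biannual interim analyses will examine the primary and secondary outcomes as well as iNCK compliance measures". Before each annual meeting the DSMB receives "a written report outlining the current status of the study, masked outcome data, and information pertaining to any adverse events". It is unmasked only on a trigger: "If the mortality difference becomes higher than 40% in either direction".

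**The concern.** Interim results by arm are normally held by a monitoring board and the statistician who reports to it, because people who run or deliver a trial may act differently once they know which way it is leaning. Here the parties named as recipients, and those further down the chain, have working roles in the trial, and the sentence puts no limit on what they may be told while it is running. If they learned comparative results, they could change who is recruited, what care control clusters receive and how events are reported. Part of the final estimate could then reflect reactions to the interim one, and this could not be undone afterwards.

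**Working it through.** The point rests on reading sections of the protocol article against each other.

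1. **Interim results are not just progress updates.** Progress updates have their own sentence. The results sentence follows it and uses the word *also*, so results are something further. The only interim analyses described cover primary outcome, secondary outcomes and compliance.

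2. **Limits on recipients differ.** The DSMB gets "masked outcome data" and is unmasked only past the 40% trigger. For AKHS,P and district leadership no masking, pooling or trigger is stated. Read literally, they could see more than the safety board does.

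3. **The cascade has no start date.** It passes on findings from the study, without saying final findings or fixing a time after follow-up.

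4. **The people in the chain have trial roles.**
 - LHWs deliver care in both arms (Study design).
 - Lady Health Supervisors hand out, and LHWs complete, the pregnancy identification forms from which women are found for screening (Delivery of the integrated neonatal care kit). This follows cluster randomization (Study design).
 - Data collectors are not blinded to allocation (Study design).
 - Omphalitis and postpartum hemorrhage information comes from participant interviews (Data collection and data management).
 - A study physician at AKHS,P evaluates adverse events, and that judgement decides whether the principal investigator is informed (Adverse event reporting).

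5. **The analysis would not remove the effect.** The primary analysis is intention-to-treat whatever the contamination (Statistical analysis plan). Adjustment for month of birth handles a trend common to both arms, not a reaction that differs by arm.

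6. **Timing.** Reading biannual as twice a year, 26 months / 6 = 4.3, so about four interim analyses fall within enrolment. These are analyses; no release schedule is given.

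7. **Size, as illustration only.** Inputs from Sample size: control risk 0.035, a 25% reduction giving 0.02625, intracluster correlation 0.002, 39 clusters of 306 per arm (39 × 306 = 11,934). Design effect = 1 + 305 × 0.002 = 1.61. Suppose a share c of control births gained the kit's full benefit:

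 control risk p0 = (1 − c) × 0.035 + c × 0.02625, and p1 = 0.02625

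 z = (p0 − p1) / √[(p0(1 − p0) + p1(1 − p1)) × 1.61 / 11,934]

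 Power is taken at two-sided 5% (sidedness is an assumption).

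| c (assumed) | p0 | Risk ratio | z | Power |
|---|---|---|---|---|
| 0 | 0.035000 | 0.75 | 3.09 | 87% |
| 10% | 0.034125 | 0.77 | 2.80 | 80% |
| 20% | 0.033250 | 0.79 | 2.51 | 71% |

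 The first row does not reproduce the stated 80% power for this size. That mismatch is a separate matter and nothing here depends on it. The table also spreads c over all control births. If a first release came at month 6 of 26, 10% overall would need 10% × 26/20 = 13% of later births, and 20% would need 26%.

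**The case against.** A reader might infer that the protocol plans to release by-arm results while the trial runs. It does not say so. The neighbouring sentence speaks of progress updates, the DSMB's data are masked, and a pooled or masked release would fit the text. This stands: the defect is a commitment without limits, not a stated unmasked release.

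A reader might also infer that LHWs and households will be told interim findings. The third sentence can be read as final findings only, and it is doubly conditional: the team recommends, and LHWs may pass results on. This stands too.

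Nor do the documents support calling AKHS,P the body that implements the intervention. They show it as a recipient of results and as the place where the study physician sits. The LHWs belong to a government programme.

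The dilution table is not an estimate. Control participants receive no kits, no route to the full benefit is shown, and the values of c are invented.

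The routes to bias have limits. All-cause death is largely objective, registering pregnancies is already an LHW duty, independent data collectors screen and enrol, and allocation is known in any case. Adverse-event relatedness is not a listed outcome. Against this, verbal autopsy separates stillbirths from early neonatal deaths and feeds the primary analysis, so the primary outcome is not wholly protected. Knowing the allocation is also different from knowing the results so far.

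Finally, who sees comparative data is often left to a board charter or full protocol. That would excuse silence, but here the article states a rule, and the rule is too wide.

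**Conclusion.** The point holds as a matter of wording. The article commits to communicating interim results to AKHS,P and district health leadership, sets no limit to pooled or masked data, and does not tie the onward cascade to final results. This is out of step with the masking it applies to its own DSMB. Release of comparative results could bias recruitment, co-intervention in control clusters, reporting of omphalitis and postpartum hemorrhage, and adverse-event judgement.

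The harm is conditional on the results being shown by arm, which the text neither states nor excludes. Its size cannot be derived from the documents. A correction is still warranted because it costs almost nothing, whereas a release cannot be reversed.

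**What to change.** - In Results dissemination, delete the words *Interim and*, so that the sentence covers final results only.
- State that by-arm interim results go only to the DSMB and the statistician who reports to it.
- State that, before database lock, AKHS,P, district leadership, Lady Health Supervisors, LHWs and government receive only pooled progress data: enrolment, follow-up and kit delivery.
- State that the cascade to supervisors, LHWs and households starts only after the final analysis.

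If any interim outcome result has already been shared, record what was shared, with whom and when. Births before and after that date could then be compared as a sensitivity analysis, although this would not remove any bias.

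The cost is a few sentences of protocol wording, and stakeholders wait for the final result. The DSMB's safety route is unaffected.

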### Confidentiality

Information obtained in the study will be securely transmitted, and the identity of the subjects will remain confidential. All records will be kept confidential in keeping with requirements as stipulated by the ethics boards of Aga Khan University, the National Bioethics Committee of Pakistan, and the Hospital for Sick Children.

## Discussion

Despite global efforts to reduce neonatal mortality, reductions in NMR remain behind what is needed to reach the SDG global target of less than 12 neonatal deaths per 1,000 in 2030 [1]. Interventions that target the most common causes of newborn deaths in high burden countries, and that are available from the time of delivery, including for home-delivered births, are crucial to reaching SDG targets [3].

GB, the northernmost administrative territory in Pakistan, has high NMRs and a large proportion of its population live in rural and remote areas. This study will deliver a portable, low-cost, easy-to-use, and evidence-based iNCK to pregnant women in GB and empower them with the knowledge needed to use the iNCK. This innovative intervention has the potential to meaningfully reduce mortality and morbidity in newborns. Moreover, utilizing Pakistan’s existing community health infrastructure to deliver the iNCK to pregnant women will inform its scale-up in similar settings with high NMR and community health worker programs.

## Data Availability

Upon completion of the study, the datasets used and/or analysed during the current study are available from the corresponding author on reasonable request and with a data sharing agreement.
